### 2.4. Clinical Assessment

Demographic data will be recorded at the measurement time point ‘pre’ before the intervention. Imaging data are used to determine the territory affected by the stroke. This will be followed by a medical history and a physical and neurological examination.

The following scales will be used to quantify neurological deficits, as assessed by trained raters before the intervention (‘pre’), at the end of the first week (T1), at the end of the second week (T2), and at the end (‘post’) of the three-week stimulation session: the Fugl–Meyer Assessment for Upper Extremity (FMAUE), an index to assess the sensorimotor impairment; the Katz Index of Independence in Activities of Daily Living (KADL) for the independence in activities of daily living (ADL); the Timed Up and Go Test (TUG) to measure mobility [26]; and the Modified Ashworth Scale (MAS) [27] and Tardieu Scale (TaS) [28] for spasticity.

The Fugl–Meyer Assessment for Upper Extremity (FMAUE) consists of 33 items with a maximum score of 66. Each item is scored on a 3-point scale of 0 points (unable to perform), 1 point (partially able to perform), and 2 points (fully able to perform). The FMAUE includes the following assessment categories: shoulder–elbow–forearm function, wrist function, hand function (subscore C), and coordination/speed [29]. The FMAUE generally has a very high inter-rater reliability, especially the subscale for upper extremity motor skills, which is used in this study [30,31,32]. This test also shows high sensitivity for patients with severe to moderate impairment [29].

The Katz Index of Independence in Activities of Daily Living (KADL) assesses the ability to perform ADLs independently in six functions, including bathing, dressing, toileting, transferring, continence, and feeding. Patients score ‘yes’ or ‘no’ for independence in each of the six functions. A score of 6 indicates full function, 4 indicates moderate impairment, and 2 or less indicates severe functional impairment [33]. The KADL has an excellent intra-rater reliability (intercorrelation coefficient, ICC= 1.000) and internal validity (ICC = 0.999) [34].

To measure mobility, the change in time for the Timed Up and Go Test (TUG) will be assessed [26]. The TUG measures the time taken for a patient to get up from an armchair, walk 3 meters, turn around, walk back, and sit down again [26]. This widely used and well-known test has very good inter- and intra-rater reliability (ICC = 0.99) [26].

Spasticity is assessed using the Modified Ashworth Scale (MAS) [27]. The MAS is a semi-quantitative measure ranging from 0 to 4 points that is used to assess the severity of spasticity. MAS scores for the shoulder, upper arm flexor wrist, and finger flexors/extensors will be evaluated for each patient. The psychometric criteria of the MAS are described very controversially in the literature, ranging from unsatisfactory to very good [35,36]. For this reason, the Tardieu scale will also be used to assess spasticity.

The Tardieu Scale (TaS) quantifies spasticity by assessing the response of the muscle to different stretch velocities and by determining the spasticity angle. A goniometer is used to measure R2 and R1. The patient is seated during the test. The stretch velocity of V1 and V3 is used to measure R2 and R1, respectively. The quality of the muscle response is also assessed using the stretch velocity of V3. The difference between R2 and R1 is used as a measure of the dynamic component of spasticity [28]. The test–retest reliability of the Tardieu scale is reported to be moderate to very good [37], with good inter-rater and very good intra-rater reliability [38].

All assessments will be recorded by therapists who are not involved in the study. Before the study starts, standardized training will be given to all those responsible for collecting the assessments. Side effects will also be recorded and compared between groups.

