### 2.2. Patient Population and Eligibility Criteria

Participation in the study is voluntary. Each patient has the right to withdraw from the study at any time without giving a reason (withdrawal of consent) and without suffering any disadvantage. The patient will be asked to state the reason for withdrawal but will be advised that he/she is not required to do so.

The inclusion criteria are stroke onset within the previous six months (defined as ‘subacute stroke’) and a relevant arm paresis with at least one point within the subscore C of the FMAUE and an MAS score of ≥1.

The exclusion criteria for this study include a history of recurrent stroke, abnormal brain findings on CT or MRI images, pacemakers or other implanted devices, metals in the affected upper extremity, a history of epilepsy in the patient’s medical history, neurodegenerative disorders, psychiatric disorders, pregnancy, the use of antispastic medication, and botulinum toxin A injections in the affected upper extremity within the previous six months. Patients will also be excluded if they have a language comprehension disorder that makes it difficult for them to understand the rationale of the study. Patients will be recruited from an inpatient neurorehabilitation clinic. All admitted patients will be screened for eligibility for the study. All eligible patients will be informed about the contents of the REPMAST. They will be enrolled when they sign the written informed consent.

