### 2.7. Outcome Measures

The primary outcome is the difference between the Fugl–Meyer Assessment for Upper Extremity (FMAUE_Diff_) scores before and after the three-week stimulation session, calculated as follows: FMAUE_Diff_ = (FMAUE_post_ − FMAUE_pre_)/FMAUE_pre_.

The secondary outcomes are KADL, TUG, MAS, and TaS, which are calculated in the same way as the primary outcome of FMAUE_Diff_.

Correlation analyses will be used to analyze the relationship between arm spasticity (MAS and TaS), arm function (FMAUE), and independence in ADL (KADL) in each intervention group (rPMS and NMS). For this reason, a sum score will be calculated for a total MAS score (MAS_total_) of all the muscles assessed. The change in this score (between pre and post, MAS_total-Diff_) and TaS (TaS_Diff_) is correlated with the change in FMAUE (FMAUE_Diff_) as well as with the change in KADL (KADL_Diff_).

For each patient, stimulation and testing will be performed at the same time from Monday to Friday between 09:00 and 12:00.

During the trial, included patients may not be enrolled in other trials, treated with botulinum toxin or antispastic drugs, receive peripheral electrical stimulation, or receive peripheral or central magnetic stimulation (see Figure 2).

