### 2.8. Statistical Analysis

Statistical analysis will be based on the intention to treat analysis using IBM SPSS Statistics 29 (IBM, Armonk, NY, USA). The Kolmogorov–Smirnov Test will be used to test for normal distribution. Levene’s test will be used to assess the equality of variances between groups. If there is no normal distribution, the Mann–Whitney-U test will be used; otherwise, analysis of variance (ANOVA) will be used to test for differences in the repeated measures of FMAUE (pre, T1, T2, and post). In this 2 × 2 factorial design, group will be the independent factor and time will be the dependent factor. Post hoc analyses will be performed for significant main effects and interactions. One-way ANOVA will be used to ensure that the baseline FMAUE scores before the test are not statistically significant between the two groups. The same analysis will also be performed for KADL, TUG, MAS, and TaS.

For the within-group analysis (pre- and post-test), a paired *t*-test will be used if the distribution is normal; otherwise, the Wilcoxon test will be used.

For FMAUE_Diff_, two-sample *t*-tests will be used to test for the difference between the two groups (rPMS and NMS) if the distribution is normal. If the distribution is not normal, the Wilcoxon test will be used. The same analysis will be used for KADL_Diff_, TUG_Diff_, MAS_Diff_, and TaS_Diff_.

To analyze the relationship between arm spasticity (MAS) and arm function (FMAUE) and independence in ADL (KADL) in each intervention group (rPMS and NMS), correlation analyses between the MAS_total-Diff_ and (TaS_Diff_) and FMAUE_Diff_ as well as KADL_Diff_ will be used.

For missing follow-up measurements, the Last Observation Carried Forward (LOCF) procedure will be applied by inserting the most recent present value before.

The level of statistical significance will be set at *p* < 0.05, and Bonferroni correction will be used for multiple comparisons.

The effect size will be calculated using Cohen’s *d* according to the formula mean difference between two groups divided by the result of the pooled standard deviation (the pooled standard deviation is calculated as (=√[(standard deviation rPMS^2^ + standard deviation NMS^2^)/2])). The effect size will be defined as small (0.2), medium (0.5), or large (0.8) [40].

The primary safety endpoint is the incidence of seizures and headaches during the intervention period.

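### TUG is scored as a proportional change in time, with no walking criterion at entry: patients unable to do the test at 'pre' get no TUG_Diff, and LOCF can hide later loss of walking

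*Protocol article*

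**What the plan says.** All references are to the protocol article.

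- **What is measured (2.4).** TUG is among the scales scheduled at 'pre', T1, T2 and 'post', with no restriction to walkers. "The TUG measures the time taken for a patient to get up from an armchair, walk 3 meters, turn around, walk back, and sit down". The variable is a time: "To measure mobility, the change in time for the Timed Up and Go Test (TUG) will be assessed".
- **How it is scored (2.7).** "The secondary outcomes are KADL, TUG, MAS, and TaS, which are calculated in the same way as the primary outcome of FMAUE_Diff". The primary outcome's formula is "FMAUE_Diff_ = (FMAUE_post_ − FMAUE_pre_)/FMAUE_pre", so TUG_Diff = (TUG_post − TUG_pre)/TUG_pre.
- **Who enters (2.2).** Besides stroke within six months, entry needs "a relevant arm paresis with at least one point within the subscore C of the FMAUE and an MAS score of ≥1". No inclusion or exclusion criterion mentions standing or walking. "Patients will be recruited from an inpatient neurorehabilitation clinic".
- **How it is analysed (2.8).** "Statistical analysis will be based on the intention to treat analysis". TUG_Diff is compared by a two-sample t-test, or a Wilcoxon test if not normal. The raw repeated TUG values go to ANOVA, or to Mann–Whitney if not normal.
- **What is done with gaps (2.8).** "For missing follow-up measurements, the Last Observation Carried Forward (LOCF) procedure will be applied by inserting the most recent present value before". No other missing-data rule is given.

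**The concern.** A timed walking test yields a number only for a patient who can stand up and walk. Inability here is not an accidental gap in the data; it is the worst state of the quantity being measured. FMAUE items in section 2.4 have a zero for inability, whereas TUG has no equivalent, and a ratio of times has no place for one.

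Two things are at stake. First, the TUG_Diff comparison shrinks to patients able to walk at 'pre', while the analysis is labelled intention to treat. A change from unable to able, which is a large mobility gain, is left out of it. Second, a change from able to unable may be replaced by an earlier and better time. That happens after randomisation, so it can differ between arms.

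This is distinct from a score of zero at baseline. A zero is an observed value that breaks a division; here there is no value at all.

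**Working it through.** **1. The stated rules applied to each type of patient.** Write t for a completed time.

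| 'pre' | later visits | TUG_Diff under 2.7 and 2.8 |
|---|---|---|
| able | able at 'post' | (t_post − t_pre)/t_pre, defined |
| unable | unable throughout | undefined: no reference value and no denominator |
| unable | able at 'post' | undefined, although t_post exists |
| able | last completed test at 'pre', then unable | if treated as missing: (t_pre − t_pre)/t_pre = 0 |
| able | last completed test at T1 or T2, then unable | if treated as missing: (t_T1 − t_pre)/t_pre or (t_T2 − t_pre)/t_pre |

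In rows 2 and 3 LOCF gives no help, because it fills follow-up values and nothing precedes 'pre'. In the last row a patient who had become faster by T2 and then lost the ability to walk is scored as improved, because t_T2 < t_pre makes the ratio negative.

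**2. The other TUG analysis in 2.8.** A repeated-measures ANOVA over the four visits also needs the 'pre' time. Mann–Whitney on raw times does not necessarily need it, so a regained 'post' time could enter there. By the stated rule that branch is used only when the data are not normally distributed, so whether regained walking counts anywhere in the TUG results would depend on a normality test.

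**3. Size.** The article states no figure for TUG. The base is the randomised total in section 2.3, which is reproduced as 120 × 1.15 = 138 (69 per group). The share unable at 'pre' is not given, so a range is assumed, equal in both arms. The standard error factor is 1/√(1 − f), with the standard deviation held fixed.

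| Assumed share f | No TUG_Diff: 138 × f | Remaining: 138 × (1 − f) | Standard error factor |
|---|---|---|---|
| 10% | 13.8, about 14 | about 124 | 1/√0.90 = 1.05 |
| 25% | 34.5, about 35 | about 103 to 104 | 1/√0.75 = 1.15 |
| 40% | 55.2, about 55 | about 83 | 1/√0.60 = 1.29 |

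As a second illustration, suppose TUG_Diff had the effect size of 0.6 that section 2.3 plans for FMAUE only, and start from the 120 evaluable patients (60 per arm, two-sided 5%, t-test). Power is 0.90 with nobody unable, 0.87 with 10% unable (54 per arm) and 0.71 with 40% unable (36 per arm). Neither the effect size nor the share is documented for TUG.

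**The case against.** The strongest objection is that the source is a condensed article. How a test that could not be performed is coded usually sits in the case report form, an assessor manual or the analysis plan, and its absence here proves nothing. That stands for the code alone. It does not dispose of the point, because the article itself fixes the ratio and the LOCF rule. A code for 'unable' held elsewhere could not be put into the ratio, so the outcome definition would have to change as well.

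Four stronger readings are tempting, and the documents do not support them.

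- **That dropping baseline non-walkers biases the comparison.** Ability at 'pre' is assessed before the intervention and cannot be caused by it, so the arms among baseline walkers are still randomised groups. The cost is precision and a narrower population than the intention-to-treat label suggests.
- **That a patient who loses walking is always scored as unchanged from baseline.** LOCF takes the most recent value, which may be T1 or T2. 'No change' holds only since the last completed test. Nor does section 2.8 say that a patient tested and unable counts as missing; that is the likely reading, but it is a reading.
- **That regained walking counts for nothing.** It is lost from TUG_Diff, but could enter the Mann–Whitney branch on raw times. The Katz Index includes transferring and may register some recovery.
- **That many patients are affected.** The article gives no number. Entry allows up to six months after stroke and requires some hand function, and no TUG difficulty is reported from the 20-patient pilot. The share could be small.

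It is also fair that TUG is one of four secondary outcomes, is not powered for, and follows stimulation of arm and hand muscles.

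**Conclusion.** The point holds in this form. With no walking criterion at entry, the stated formula leaves TUG_Diff undefined for anyone unable to do the test at 'pre', and walking regained by 'post' is left out of that comparison. If later inability is treated as missing, the stated LOCF rule replaces it with the last completed time, and this can differ by arm. The second effect is the one that can distort the between-arm result; the first costs precision and scope.

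The size is unknown: about 14 to 55 of 138 patients without a TUG_Diff if 10% to 40% are unable at 'pre', a range that is assumed and not documented. The number who lose walking during the three weeks is not given either. The primary outcome and the figures of 120 and 138 are untouched. This is a correction worth making to a secondary outcome, not a threat to the trial's main conclusion.

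**What to change.** 1. Record 'unable' as an outcome code for TUG at every visit, separate from 'not tested'. This must be done at the visit, since the two may not be distinguishable afterwards.
2. Compare TUG between arms with a rank-based analysis in which 'unable' takes the worst rank, so that regained and lost walking both count and no division by a baseline time is needed.
3. Do not apply LOCF to visits where the patient was tested and could not perform. These are observed outcomes.
4. Report the number able to complete the test by arm and visit.
5. Show times, or change in seconds, descriptively among those able at both 'pre' and 'post', labelled as a subset and not as intention to treat.

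Converting the result to a speed (6 m divided by TUG time, with zero for unable) is less suitable, because the time includes rising, turning and sitting and the quotient is not a walking speed.

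The cost is one case report form code and revised outcome and analysis wording, with no new visit or procedure. The small downside is that the main TUG comparison is no longer expressed in seconds. If the sponsor prefers to keep the present formula, the minimum is to state that TUG_Diff applies only to patients able at 'pre' and to report how many in each arm were not. That would still leave the LOCF problem to be settled.

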### 2.5. Randomization and Blinding

We will use a blocked randomisation procedure. Eligible patients will be blindly randomized into one of two groups, the rPMS group or the NMS group, using a randomization box with opaque sealed envelopes. An independent and impartial person will carry out the randomisation procedure (1:1 allocation ratio). The assessments are collected by neutral therapists who are not involved in the study. The person administering the stimulation is not involved in the motor testing. The therapists providing the rehabilitation therapy are also blinded to the patients’ affiliation. The data analyst is unaware of the patients’ allocation.

### 2.6. Treatment

#### 2.6.1. Repetitive Peripheral Magnetic Stimulation (rPMS)

For rPMS, a figure-of-eight coil of MAGSTIM Rapid² will be used with a maximum magnetic field strength of 0.5–3.5 Tesla.

The patient will be seated during the stimulation. Stimulation begins with the arm flexors, then the arm extensors and the hand flexors, and it ends with stimulation of the hand extensors. The coil will be positioned flat along the muscle belly to induce large amplitudes of electrical current [39]. Before starting the stimulation session, the passive range of motion (pROM) of the elbow and hand will be determined. The stimulation intensity will be adapted to each patient and will depend on two criteria. First, the stimulation must be painless. If a patient finds the stimulation painful, the stimulation intensity will be reduced in 5% increments until the patient tolerates the stimulation intensity. Second, the stimulation intensity must be at least half the pROM of the muscle contraction. The stimulation intensity will be started with an intensity at 20% of the maximum stimulator output and increased or decreased in 5% increments. Patients who cannot tolerate sufficient stimulation intensity to induce a half pROM muscle contraction will be excluded.

The 20 Hz rPMS is applied in four trains. Each train consists of 25 bursts of 40 pulses. Each patient receives a total of 4000 pulses in a 13 min stimulation session (see Figure 1). Patients will receive one stimulation session per day, five days per week, from Monday to Friday, for three weeks, for a total of 15 stimulation sessions, with clinical assessment after the last stimulation day (post).

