#### 2.6.2. Neuromuscular Stimulation (NMS)

In the NMS group, the electrical stimulation will be delivered using Wellcare Digi-Stim^®^ (Sanowell, Alzenau, Germany) with 4.0 × 4.0 cm^2^ electrodes placed on the skin. The patient will be seated during electrical stimulation. Electrical stimulation will start with the flexors and then the extensors of the arm and the hand. The same two criteria as in the rPMS group will be used to determine the stimulation intensity: a painless stimulation and a muscle contraction of at least 50% pROM. The stimulation frequency of the electrical stimulation will be 20 Hz, with an on phase of two seconds and an off phase of three seconds. Each muscle group will receive 25 muscle contractions in a 12 min session. Patients will be stimulated daily from Monday to Friday for three weeks, for a total of 15 stimulation sessions.

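### The rule excluding patients who cannot tolerate enough rPMS intensity reads as a one-arm, post-randomisation exclusion and is not reconciled with the intention-to-treat analysis

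*Protocol article*

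**What the plan says.** All references are to the protocol article.

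- **Section 2.6.1 (rPMS).** Intensity is titrated on the magnetic stimulator: "The stimulation intensity will be started with an intensity at 20% of the maximum stimulator output and increased or decreased in 5% increments". The consequence of failing is then stated: "Patients who cannot tolerate sufficient stimulation intensity to induce a half pROM muscle contraction will be excluded".
- **Section 2.6.2 (NMS).** "The same two criteria as in the rPMS group will be used to determine the stimulation intensity". Nothing is said about an NMS patient who cannot meet them.
- **Section 2.2 (eligibility).** The list that begins "The exclusion criteria for this study include a history of recurrent stroke, abnormal brain findings on CT or MRI images" does not include intolerance of stimulation. On enrolment: "They will be enrolled when they sign the written informed consent".
- **Section 2.5 (randomisation).** "Eligible patients will be blindly randomized into one of two groups, the rPMS group or the NMS group". No tolerance test or run-in before allocation is described.
- **Section 2.8 (analysis).** "Statistical analysis will be based on the intention to treat analysis", with last observation carried forward (LOCF) for missing follow-up.

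No section says whether exclusion means from stimulation, from follow-up or from the analysis.

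**The concern.** An intention-to-treat comparison keeps every randomised patient in the allocated group. A rule that takes patients out because the allocated device did not work for them selects on something observed after allocation. If it acts in one arm only, tolerators in that arm are compared with everyone in the other.

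Applying the rule in both arms would not fully restore balance. Pain and evoked contraction are judged on two different devices, so different patients would be removed. The judgement is also made during treatment, with the device in view, so the assessor and analyst blinding in section 2.5 does not cover it.

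The primary superiority comparison is at stake. Assessments not made on excluded patients cannot be recovered later by an analysis plan.

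**Working it through.** **1. When and where the rule acts.** Patients are enrolled at consent (2.2), and eligible patients are then randomised (2.5). Intolerance is not an eligibility item. The rule sits in the arm-specific treatment section and depends on titration in percent of the magnetic stimulator's output. Exclusion after allocation in the rPMS arm is therefore the natural reading, but it is an inference: section 2.6.1 does not give the timing.

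**2. The plan's own figures (2.3).** Inputs: effect size 0.6, power 90%, two-sided 5%. The two-sample t-test needs 59.35, so 60 per arm or 120 in total, as stated. Then 120 × 1.15 = 138, or 69 per arm, also as stated.

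**3. If excluded patients leave the analysis.** Let q be the share of intolerant patients and m the amount, in SD, by which their outcome is worse than that of the others. With everyone kept, the rPMS mean is (1 − q) × μ + q × (μ − m) = μ − q × m. With intolerant patients removed, it is μ. Hence bias = q × m, toward rPMS when m is positive and away from it when m is negative.

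Under no true effect, z = q × m / √(1/(69(1 − q)) + 1/69). For q = 0.10 and m = 1: 0.10 / √(1/62.1 + 1/69) = 0.10 / 0.175 = 0.57, which gives a two-sided error of 8.8%. For q = 0.20 and m = 1: 0.20 / √(1/55.2 + 1/69) = 0.20 / 0.181 = 1.11, which gives 19.8%.

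The other rows come from simulation (69 per arm, 40,000 runs each, removal from rPMS only). Both q and m are assumptions throughout.

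| Share q | Gap m (SD) | Bias q × m (SD) | Two-sided type I error |
|---|---|---|---|
| 5% | 0.3 | 0.015 | 5.1% |
| 10% | 0.5 | 0.05 | 5.8% (5.9% by formula) |
| 20% | 0.5 | 0.10 | 8.4% (8.6% by formula) |
| 20% | 0.8 | 0.16 | 13.5% |
| 10% | 1 | 0.10 | 8.8% (formula) |
| 20% | 1 | 0.20 | 19.8% (formula) |

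With all patients kept, the simulated error stays at about 5%.

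**4. If excluded patients stay in the analysis but are not followed.** A patient who leaves before T1 has only the 'pre' score. LOCF puts it in place of 'post', so by the definition in 2.7 the outcome is (pre − pre)/pre = 0. If such patients would have changed by μ_I on average, the rPMS mean shifts by −q × μ_I. Where patients generally improve, this works against rPMS.

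**5. If the rule acts in both arms.** The bias is q₁m₁ − q₂m₂ (rPMS minus NMS). It is smaller, and vanishes only if the two products agree. With a gap of 0.5 SD and assumed shares of 10% and 5%, it is 0.05 − 0.025 = 0.025 SD.

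**6. Power.** On top of the planned 15% drop-out, removing 5%, 10% or 20% of the rPMS arm leaves power at 88.9%, 88.0% or 85.9% for an effect of 0.6. Power loss is minor; bias is the issue.

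**The case against.** The strongest defence is that 'excluded' is undefined. If it means only that stimulation stops, while the patient is still assessed and analysed as allocated, the rule and intention to treat are compatible. That stands: a reader might infer that the two cannot coexist, but they conflict only if patients leave follow-up or the analysis. However, no passage keeps these patients under assessment, so the defence relies on wording that is absent.

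Second, the one-arm reading rests partly on silence. Section 2.6.2 imports the same two criteria, and a condensed article may state the consequence once. This also stands in part. The criteria are shared to set intensity, but the consequence is not stated for NMS, and a two-arm rule would still remove randomised patients.

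Third, a reader might infer that the bias must favour rPMS. The document does not say that intolerant patients do worse, and its own LOCF rule can push the other way.

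Fourth, the larger error rates need extreme inputs. A 1 SD gap exceeds the whole planned effect of 0.6, a 20% share exceeds the planned 15% drop-out, and the introduction describes rPMS as painless. This is fair: the 19.8% figure is the edge of the assumed range, not an expectation.

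Finally, it would be wrong to call those who remain rPMS responders. The criterion is a tolerable evoked contraction, not a gain on the FMAUE.

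**Conclusion.** The point holds in limited form. Section 2.6.1 states an exclusion rule that, on its natural reading, acts after randomisation in the rPMS arm. It conflicts with section 2.8 if it means removal from follow-up or analysis. It is a stated rule, not a detail left to another document. Followed as written, it either removes randomised patients selectively or, if they leave before T1 and are kept by LOCF, fixes their primary outcome at zero.

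Timing, scope and the meaning of exclusion are inferred. The direction of bias is open. If patients are removed from rPMS only, with 5% to 20% excluded and outcomes 0.3 to 1 SD worse (all assumed), the bias is about 0.015 to 0.20 SD. The upper end is one third of the planned 0.6. The two-sided type I error runs from about 5%, practically nominal, to about 20%. The document does not support any particular value in that range.

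**What to change.** Reconcile sections 2.6.1, 2.6.2 and 2.8:

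- Every randomised patient stays in the primary analysis in the allocated group, is assessed at T1, T2 and 'post', and is not replaced, whether or not the intensity criterion is met.
- Failure to reach the criterion is recorded in the same way in both arms.
- A per-protocol analysis with the same rule in both arms may be added as support only.

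If tolerance is in fact tested before allocation, say so in sections 2.2 and 2.5 and apply the test to all patients.

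The cost is a change of wording and keeping the scheduled assessments for the patients concerned. The downside is slight dilution of the effect. No stimulation rule is proposed here.
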